#### List of pre-specified “key time segments” for patients with advanced peripheral artery disease

Symptom onset to admission

Admission to ABI/TBI measurement

Admission to IV heparin administration

Admission to vascular specialist at bedside

Admission to revascularization

Length of stay (days)

### Study outcomes

The study outcomes that will be evaluated are summarized in Table 2. The systemic ischemic risk clinical outcomes include: nonfatal MI, nonfatal stroke, cardiovascular (CV) death, all-cause death, and cardiovascular re-hospitalization event rates. The limb ischemic risk clinical outcomes include: ALI or CLI recurrence, minor or major amputation, and total amputation event rates. These individual outcomes will be used to derive a composite triple endpoint (defined as any nonfatal MI, stroke or amputation) and quadruple endpoint (defined as any non-fatal MI, stroke, amputation or death). As well, the relevant clinical outcome of “amputation-free survival” time will be calculated at one year.

**Table 2 T2:** Clinical evaluations on admission and at 1-, 6- and 12-month follow-up

		**Admission**	**Hospital discharge**	**1 month**	**6 month**	**12 month**
**Demographic, clinical and functional characteristics, and key time segments**						
Demographic variables						
	Race, gender, education	X				
	Marital and employment status	X	X	X	X	X
Physical examination (weight, height, blood pressure, heart rate and rhythm)		X				
Laboratory values (serum creatinine, hemoglobin, fasting lipid profile)		X				
Etiology of ALI-CLI		X				
Key time segments (see ‘List of key time segments’)		X	X			
Length of hospital stay			X			
Endovascular and open surgical procedures			X			
Ambulatory status		X	X	X	X	X

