In this context, specific knowledge gaps regarding determinants of adverse health outcomes for individuals with ALI and CLI were used to design a hypothesis-driven clinical registry. The primary aim of the FRIENDS registry is to evaluate a pre-defined set of patient and health system factors on one-year rates of systemic and limb ischemic events, and thus on amputation-free survival. These factors included: (i) pre-hospital limb ischemia symptom duration, (ii) use of leg revascularization strategies, and (iii) use of risk-reduction pharmacotherapies. Outcome events (rates of non-fatal MI, stroke, amputation, and death) will be collected at one month, six months, and one year. Secondary study aims are to assess: (a) the relative frequency and etiology of the ALI and CLI diagnoses in a large community-derived population, (b) the frequency of use of evidence-based risk-reduction medication in this high-risk population at baseline and during follow-up, (c) predictors of functional status, and (d) rates of systemic ischemic events. The FRIENDS registry structure was *pre hoc* designed to serve as a pilot study for future implementation of a multicenter registry to prospectively evaluate the impact of standards of care on health outcomes for all individuals with ALI and CLI.

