### Definition of advanced PAD syndromes

The registry was designed to utilize definitions of advanced PAD (ALI and CLI) that are encompassed in the intersocietal “ACC/AHA Guidelines for the Management of Patients with PAD” [1] and concordant TASC-II [2] PAD guidelines. As such, ALI is clinically defined by the admitting vascular specialist in patients who experience the clinical stigmata associated with acute ischemia and a potential threat to limb viability of less than or equal to 14 days in duration. Using this guideline-derived ALI case classification, enrollment of patients is achieved via documentation of acute limb ischemic symptoms and signs (the 6 “Ps”) (Table 1). CLI will be defined, per these PAD clinical care guidelines, in patients with Rutherford class 4, 5, or 6 manifestations such as ischemic rest pain, and minor or major tissue loss of greater than two weeks duration. At enrollment, patients with ALI and CLI will undergo evaluation of an objective pedal or toe pressure measurement when this is feasible pre-revascularization. Source documents have been created so that collection of these entry criteria, as applied by participating clinicians, will be uniformly obtained.

**Table 1 T1:** Inclusion criteria: Ischemic symptoms and signs, and objective limb pressure measurements at enrollment

**For all patients: Clinical symptoms and signs**	**For ALI patients: Presence of any of the “6 Ps”**	**For all patients: Objective pressure measurements**
Ischemic rest pain	Pain	Pedal pressures
Ulcer	Pale	Great toe pressures
Gangrene	Pulseless	Ankle-brachial index
	Paresthesia	Toe-brachial index
	Paralysis	
	Poikilothermia	

*Abbreviations*: *ABI* Ankle-brachial index, *TBI* toe-brachial index.

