### Use of source documents and data abstraction

This is a prospective registry, and as such all sequential eligible patients with ALI or CLI who are hospitalized (defined as requiring an index leg revascularization procedure or overnight stay) will be entered into the registry. Medical record documentation will be required immediately on admission (not retrospectively) for establishment of the presence of ALI or CLI. Vascular specialty and hospitalist staff will receive instruction on: (a) the clinical definitions of ALI and CLI, (b) how to complete a source document on patient admission that includes the time of onset of symptoms, and (c) the use of health system tools (e.g., standardized order sets) to facilitate prompt measurement of pedal or great toe pressures (Table 1).

A documented medical history of coronary artery disease (CAD) will consist of 1 or more of any of the following chart documented conditions or procedures: stable angina, previous myocardial infarction, history of percutaneous coronary intervention or history of coronary artery bypass graft surgery. Documented cerebrovascular disease (CVD) will be defined by a history of transient ischemic attack (TIA), ischemic or hemorrhagic stroke, carotid stenting or carotid endarterectomy. Documented prior PAD will be defined by 1 or more of the following criteria: symptomatic PAD defined by history of claudication, asymptomatic PAD documented in the medical records, or history of ALI or CLI.

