### Key time segments

The symptom onset of an initial episode of ALI/CLI is defined by the patient’s self-report provided to the vascular specialist at hospital admission, is dictated into the encounter note, and this note (date and time) is later abstracted from the medical records. Vascular specialists (vascular surgeons, vascular medicine specialists, and interventional radiologists) are instructed to document the patient-reported index limb symptom onset within pre-specified time parameters: within one hour for patients presenting within 3 days, within one day for patients presenting within 3 to 30 days, and within one week for patients presenting greater than one month since symptom onset. For CLI patients who cannot state an exact time of leg symptom onset, it will be assumed that the onset time is 12 noon on the day specified. Inasmuch as ALI or CLI is known to recur (repeat episodes are common), the index leg symptom is arbitrarily defined as that which is temporally closest to the index hospitalization. This approach is similar to that used for ACS or stroke health services research.

While the pre-admission symptom duration serves as the primary pre-defined hypothesized predictor of advanced PAD health outcomes, a number of other clinical care time segments are considered of potential utility in evaluation of the efficiency of hospital-based PAD care, as it is known that CLI hospitalizations are lengthy (greater than seven days) and expensive [15]. The “admission to ABI/TBI” time segment is defined as the time from hospital arrival to initiation of the first hospital-based pedal or toe pressure measurement. The “admission to heparin” time is defined as the time from hospital arrival to the chart-documented initiation of a therapeutic intravenous heparin infusion for patients so treated. The “admission to vascular specialist at bedside” time segment is defined as the time from hospital arrival until the patient is evaluated by a vascular specialist, and this is set by the time of the dictated note. The “admission to revascularization” time segment is defined as the time from hospital arrival until the patient enters the operating room or catheterization laboratory, and includes only the use of an endovascular procedure, surgical procedure or primary amputation (medical treatment alone is not included in this definition). Hospital length of stay is defined as the number of days of hospitalization from admission to discharge.

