### Statistical analysis

Descriptive statistics will be presented as means and standard deviations for continuous variables, and frequencies and percentages for categorical data. Continuous data that are not normally distributed will be analyzed by nonparametric methods. Key time variables will be analyzed as continuous variables, and also categorized to allow assessment of dose–response patterns. Univariate models for all outcome variables with demographic, clinical and risk factor variables will be used to elucidate potential confounding variables. Multivariable logistic regression models will be used to assess the association between key time variables and short-term binary outcomes (amputation, MI, stroke and death), with adjustment for confounders. Survival analysis will be performed using Kaplan-Meier methods for preliminary analyses, and Cox proportional hazards models with adjustment for confounders. Multiple linear regression models will be used to assess the associations between time segment variables and length of stay, with adjustment for confounders. A two-sided p-value of <0.05 will be considered statistically significant. Data analysis will be performed using Stata (Stata Inc, College Station, TX, USA).

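### The stated confounder rule does not guarantee adjustment for limb severity or ALI/CLI in the revascularization-strategy and in-hospital delay analyses

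*Protocol article*

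**What the plan says.** All references are to the protocol article.

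- **Exposures.** The Background gives three pre-specified factors, the second being "ii) use of leg revascularization strategies". Table 2 records it at hospital discharge as "Endovascular and open surgical procedures". Key time segments adds in-hospital segments from arrival to heparin, to the vascular specialist and to revascularization. The last runs "until the patient enters the operating room or catheterization laboratory".
- **Severity at entry.** Definition of advanced PAD syndromes enrols CLI as "patients with Rutherford class 4, 5, or 6 manifestations such as ischemic rest pain, and minor or major tissue loss". Table 1 lists rest pain, ulcer, gangrene, the six acute signs for ALI, and limb pressures. The text adds: "Source documents have been created so that collection of these entry criteria, as applied by participating clinicians, will be uniformly obtained". Pressures are taken when feasible, and the Discussion confirms that they are not required for inclusion.
- **Adjustment.** Statistical analysis looks for potential confounders by running univariate models of each outcome on variables classed as demographic, clinical or risk factor. Logistic models then relate the time variables to amputation, MI, stroke and death, and survival is analysed by "Cox proportional hazards models with adjustment for confounders". No covariate is named as always included, and no screening threshold is given.
- **Size.** Determination of sample size reports no power analysis and gives no target number.

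**The concern.** Treatment strategy and speed of treatment are decisions made by people who have examined the limb. Severity therefore plausibly affects the exposure, and it also predicts amputation and death. A variable of that kind belongs in the model because of how the exposure is assigned. A rule that looks only at the outcome does not ask that question, and in a small sample it can drop the variable by chance.

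If severity drops out, a strategy used more often in worse limbs looks harmful. Quick treatment of the most threatened limbs makes delay look harmless or even protective. The registry exists to find care-delivery targets for later trials, so either result could point those trials the wrong way.

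Symptom duration before admission is different. Severity at admission may be a consequence of that exposure, so the argument does not extend to it.

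**Working it through.** The plan states no sample size, event count or power to reproduce. The figures below illustrate the possible size. The inputs are assumptions, except that the assumed failure rates can be compared with the Discussion's reported ranges (annual amputation in CLI 10% to 40%; 30-day major amputation in ALI 10% to 30%). All three steps were recalculated for this review.

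**1. Strategy, no true effect, severity left out.** Let p be the share with tissue loss, and a1 and a0 the proportions having open surgery with and without it.

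- Severe share among open cases: p·a1 / (p·a1 + (1−p)·a0). The share among endovascular cases uses 1−a1 and 1−a0.
- Crude risk in a group: severe share × severe risk + (1 − severe share) × milder risk.
- Base case, p = 0.5, a1 = 0.6, a0 = 0.3, one-year failure 40% vs 15%: severe shares 0.30/0.45 = 0.667 and 0.20/0.55 = 0.364. Crude risks are 0.667×0.40 + 0.333×0.15 = 31.7% and 0.364×0.40 + 0.636×0.15 = 24.1%. OR = (0.317/0.683)/(0.241/0.759) = 1.46.
- Weak selection (50% vs 40% open, same risks): shares 0.556 and 0.455, risks 28.9% and 26.4%, OR 1.13.
- Strong selection (70% vs 30% open, failure 40% vs 10%): shares 0.70 and 0.30, risks 31.0% and 19.0%, OR 1.92.
- If the severe shares are equal, the OR is 1.00. The bias depends wholly on an imbalance that the document does not give.

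**2. Delay, no true effect.** Logistic regression of amputation on log2 delay, simulated with n = 400,000, log-SD of delay 0.8, 30% severe limbs and amputation 30% vs 10%.

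| Severe limbs treated sooner by | OR per doubling, severity omitted | OR with severity added |
|---|---|---|
| 2-fold | 0.81 | 1.00 |
| 3-fold | 0.76 | 1.00 |
| 6-fold | 0.75 | 1.00 |

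**3. How often the stated rule would miss severity.** Severity 30% of limbs, amputation 30% vs 10%, chi-square screen at p<0.05. The threshold and the sample sizes are assumptions.

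| n | Severity screened out |
|---|---|
| 100 | about 31% |
| 150 | about 16% |
| 200 | about 7% |
| 400 | under 1% |

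Steps 1 and 2 give the bias with no adjustment at all. The screen drops severity when its association with outcome is weak in that sample, so the bias in those samples would on average be smaller. The figures in steps 1 and 2 are best read as upper limits for their inputs.

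**The case against.** The case on the other side is substantial.

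- **Severity is collected.** A reader might infer from Table 2, which has no row for Rutherford class, tissue loss or acute signs, that limb severity is not recorded. The document does not support that. Table 1 and the accompanying text put these items on uniform source documents. Table 2 is a visit schedule that also lacks rows for age and for the ALI/CLI diagnosis.
- **Adjustment is planned.** A reader might also infer that the analyses are confounded as designed. That is too strong. Severity is plainly a clinical variable, nothing excludes it from the screen, and the logistic, Cox and linear models are all adjusted.
- **A strong confounder is usually found.** With 100 patients per stratum and failure of 40% vs 15%, a univariate test at 0.05 has about 98% power. Severity strong enough to cause the larger biases would normally be screened in once the cohort reaches a few hundred.
- **Covariate lists often sit in an analysis plan, and none is shown here.** This is fair as far as unnamed covariates go. The article does state a selection rule, however, and the rule is what is questioned.
- **The prior-PAD definition** omits earlier leg revascularization and amputation. It says when prior PAD counts as present and is not an inventory of history items, so it does not show that these go unrecorded.

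These arguments remove any claim that severity is missing or excluded. They leave one gap: the stated rule does not commit to severity, or to ALI versus CLI, in the models where the reason to adjust is known in advance. Nor does describing the registry as hypothesis-generating close that gap, because the hypotheses it passes on are what this bias would distort.

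**Conclusion.** The point holds in a limited form. Selecting confounders by univariate association with outcome does not guarantee that entry severity or ALI/CLI enters the models for revascularization strategy and in-hospital delay. Those analyses are open to confounding by indication and triage; the document does not show that they are confounded.

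The risk is mainly one of a small cohort: under the assumed inputs and screen, about 31% of samples of 100 would omit severity, and under 1% of samples of 400. If it were omitted, the spurious odds ratio could reach 1.13 to 1.92 for strategy and 0.81 to 0.75 per doubling of delay. These sizes rest on assumed selection, assumed risks, an assumed threshold and assumed sample sizes. Because the data are already planned, this is a free improvement.

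**What to change.** Add one sentence to Statistical analysis. In every model of revascularization strategy, and of the admission-to-heparin, admission-to-specialist and admission-to-revascularization segments, ALI/CLI and recorded entry severity enter as forced covariates or strata, whatever the univariate result. Entry severity means Rutherford class or tissue loss for CLI and acute signs for ALI.

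Two limits should be written in:

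- **Limb pressure in a sensitivity analysis only.** It is not required for inclusion and may be selectively missing.
- **Severity not forced into the symptom-duration models.** There it may be a consequence of the exposure, and adjusting could remove part of the effect under study.

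The cost is a few degrees of freedom, which is felt most in a small cohort. No new data collection is needed. Table 1 names no graded ALI severity class, so adjustment within ALI rests on the acute signs and some residual confounding may remain.

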**Risk factors and risk-reduction therapies**						
Historical risk factors		X				
Use of risk-reduction pharmacotherapies		X	X	X	X	X
Smoking status		X	X	X	X	X
**Outcome events**						
Amputation (major or minor)			X	X	X	X
Cardiovascular ischemic events (non-fatal MI and stroke), death			X	X	X	X
Recurrence of ALI-CLI			X	X	X	X
Other causes of hospitalization				X	X	X

“Minor amputation” is defined as removal of any part of the lower limb below the ankle and “major amputation” is defined as removal of part of the lower limb above the ankle. All-cause death is ascertained via the social security death index (SSDI) in the USA or via other national death registry systems using a combination of the social security number (SSN), name and birth date to identify cases. Searching the online SSDI, with a correct SSN provides an accurate method to determine death as an outcome in clinical research studies. A majority of subjects ordinarily lost to followup including those with sudden death outside the hospital can thus have their vital status accurately determined [16]. Cardiovascular death includes fatal stroke, fatal MI, and other cardiovascular death. Other cardiovascular death includes deaths of cardiac origin: death associated with pulmonary embolism, vascular operation or procedure, amputation (except for trauma or malignancy), heart failure and visceral or limb infarction. Re-hospitalization for CV events is defined as hospitalization for transient ischemic attack, unstable angina, worsening of PAD, CHF, other ischemic arterial event or bleeding leading to both hospitalization and transfusion. Recurrence of ALI/CLI is defined as occurrence of any second episode of clinically diagnosed ALI/CLI and ascertained by medical chart review at follow-up.

Follow-up will be performed primarily by phone calls at 1 month (with a one week window), 6 months (with a one month window), and 12 months (with a two month window) after hospital discharge using a phone script containing standardized questions. The occurrence of non-fatal MI, non-fatal stroke, amputation, re-hospitalization, recurrence of ALI/CLI are ascertained by medical records, all cause death by social security death index website [17], and CV death by medical record review. Ambulatory status will be ascertained by self-report during follow-up calls and at return visits.

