## Discussion

It is well-known that patients presenting with advanced PAD bear a high burden of systemic ischemic events and suffer an adverse limb prognosis, with very high health economic impact [18]. Thus, care for patients with advanced PAD is a critical public health issue in the USA and internationally [19]. Current epidemiological data suggest that the incidence of ALI is 130 to 160 per million per year [3,7] and the incidence of CLI is approximately 340 to 1000 per million per year [2,4]. Major amputation rates at 30 days after clinical presentation have been reported to be 10-30%, and death at one year is reported to range from 16-42% for ALI patients [7,20]. Patients with CLI face a comparably dismal prognosis and the annual amputation rate has been reported to vary between 10% and 40% after a first diagnosis of CLI [21]. Overall, one- and five-year mortality rates of patients with CLI are reported to be 20-25% and 40-70%, respectively [22-24]. There are few cardiovascular diseases with such adverse short-term outcomes. However, diseases with high rates of adverse short term outcomes are favorable for study within a disease registry frame.

The FRIENDS Registry was designed to enroll a high volume of sequential patients with advanced PAD in order to collect an adequate sample to permit evaluation of the contributions of patient demographics, PAD etiology (e.g., cardioembolism vs. graft failure), key time segments, use of risk-reduction medications, and revascularization strategies on functional status, rates of revascularization, amputation, systemic ischemic event rates, and death. These data will also provide the opportunity to determine how clinicians in practice assess patients with advanced PAD in real world (not clinical trial) settings, including data that might define rates of adherence to current evidence-based clinical care guidelines.

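### The only stated anchor for the 1-, 6- and 12-month assessments is hospital discharge, so a one-month outcome taken at contact has a risk window that grows with length of stay and biases the in-hospital time-segment associations

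*Protocol article*

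**What the plan says.** In the protocol article, the follow-up paragraph after Table 2 reads "Follow-up will be performed primarily by phone calls at 1 month (with a one week window"; the last call is at "12 months (with a two month window) after hospital discharge". The next sentence says that non-fatal events "are ascertained by medical records, all cause death by social security death index website".

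Table 2 marks the amputation row and the row "Cardiovascular ischemic events (non-fatal MI and stroke), death" at hospital discharge as well as at 1, 6 and 12 months, so in-hospital events count.

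The Background (primary aim) and Study outcomes name horizons without an origin. Amputation-free survival "time will be calculated at one year", but the text does not say from when.

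The list of key time segments has six entries: symptom onset to admission; admission to ABI/TBI, to heparin, to vascular specialist and to revascularization; and length of stay. The Statistical analysis section uses multivariable logistic regression for the "association between key time variables and short-term binary outcomes". It also plans Kaplan-Meier and Cox analyses, again without a stated origin.

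**The concern.** A logistic model of a yes/no outcome treats every patient as observed for the same time. If one-month status is read at a contact one month after discharge, and in-hospital events are included, a patient with a long stay has been at risk for longer than a patient with a short one. That matters little for a predictor unrelated to the stay. Here, however, one listed predictor is the stay itself, and four others are intervals that begin at arrival and normally lie within it. A slow in-hospital pathway lengthens the stay, the stay lengthens the window, and the window raises the event count.

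The plan also categorises the time variables to look for dose-response. The artefact would produce one, in a registry meant to identify health-system targets and to supply effect estimates for later trials.

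**Working it through.** The document states no sample size, event count or effect for this analysis, so there is no figure of its own to reproduce. The check asks how large an association appears when there is none.

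**Inputs from the document**
- Contacts at 1, 6 and 12 months after discharge (follow-up paragraph).
- In-hospital events counted (Table 2).
- 30-day risk of 10–30%: "Major amputation rates at 30 days after clinical presentation" (Discussion).
- One-year death of 16–42% for ALI and 20–25% for CLI, and annual CLI amputation of 10–40% (Discussion).
- Stay: "CLI hospitalizations are lengthy (greater than seven days" in the Key time segments section, with no distribution given.

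**Assumptions**
- Stays of 3 to 21 days.
- The hazard shapes given below.
- The same hazard in every patient, so no true effect.

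**One month, constant hazard.** The window is length of stay + 30 days, and risk = 1 − (1 − r)^(window/30), where r is the 30-day risk.

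| r | Stay 3 vs 7 days | Stay 3 vs 14 days | Stay 7 vs 21 days |
|---|---|---|---|
| 10% | 10.9% vs 12.2%, OR 1.13 | 10.9% vs 14.3%, OR 1.36 | 12.2% vs 16.4%, OR 1.41 |
| 20% | 21.8% vs 24.1%, OR 1.14 | 21.8% vs 27.9%, OR 1.39 | 24.1% vs 31.6%, OR 1.46 |
| 30% | 32.5% vs 35.6%, OR 1.15 | 32.5% vs 40.7%, OR 1.43 | 35.6% vs 45.5%, OR 1.51 |

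One cell in full: r = 20% gives a daily rate of −ln(0.8)/30 = 0.00744. For a 7-day stay, 1 − exp(−0.00744 × 37) = 24.1%. For a 21-day stay, 1 − exp(−0.00744 × 51) = 31.6%. The odds ratio is (0.316/0.684)/(0.241/0.759) = 1.46.

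**One month, falling hazard.** Suppose the rate drops to one third (0.00248 per day) after day 30. For a 7-day stay, 1 − 0.8 × exp(−0.00248 × 7) = 21.4%. For a 21-day stay, 1 − 0.8 × exp(−0.00248 × 21) = 24.1%. The odds ratio is 1.17, so the artefact shrinks but does not vanish.

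**Later contacts, same constant-hazard method.**
- 6 months, one-year risk 20–40%: OR 1.02 to 1.09.
- 12 months, one-year risk 16–42%: OR 1.01 to 1.05, a risk difference of 0.2 to 1.2 percentage points.

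**Simulation with no true effect.** 200,000 patients; admission to revascularization averaging 2 days and stay averaging 8 days (both assumed); event time independent of every delay; 30-day risk 20% for the 30-day analysis and one-year risk 25% for the 365-day analysis. Odds ratios are per 7 days of the predictor.

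| Predictor | Discharge + 30 d | Admission + 30 d | Discharge + 365 d | Admission + 365 d |
|---|---|---|---|---|
| Admission to revascularization | 1.21 | 0.98 | 1.02 | 1.00 |
| Length of stay | 1.22 | 0.99 | 1.02 | 1.00 |
| Pre-admission delay, unrelated to stay | 1.00 | 1.00 | 1.00 | 1.00 |

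A fixed window from admission removes the association; the remaining departures from 1 are simulation noise. One simplification is that the stay is not cut short by the event. In practice an in-hospital death ends the stay, which pulls the length-of-stay association the other way, so these values illustrate the mechanism and do not forecast the registry's result.

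**The case against.** The strongest reply is that the discharge-anchored sentence schedules telephone calls and does not define an outcome clock. Events come from medical records and a death index, which can date them independently of any call. The origin of a survival analysis and the definition of a short-term outcome are details that an article may leave to a fuller document. Much of this stands: the article does not say that outcomes are timed from discharge, and a Cox model from admission with dated events would avoid the artefact.

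The reply does not remove the point. Discharge is the only anchor the article attaches to these time points, and the logistic model is stated. The only other post-admission assessment before six months in Table 2 is at discharge itself, which would make the window the stay alone.

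Four stronger readings are tempting and not supported:

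- **The clock starts at discharge and in-hospital events are lost.** Table 2 records outcome events at discharge. Under that reading the window would also be fixed and would not grow with stay; the simulation gives an odds ratio of 1.00 for admission to revascularization when only post-discharge events are counted.
- **Delay is tied to outcome by construction for the main hypothesis.** The primary predictor ends at admission and is no part of the stay. The plan will examine how time segments relate to stay, but the document gives no correlation between pre-admission duration and stay.
- **One-year amputation-free survival is seriously distorted.** The 12-month odds ratios of 1.01 to 1.05 do not bear that out.
- **The registry's rates cannot be set against any published rate it cites.** Only the 30-day amputation figure is expressly timed from presentation, the CLI amputation rate runs from first diagnosis, and no formal comparison is planned.

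**Conclusion.** The point holds in a limited, conditional form. If one-month status at contact is what enters the logistic regression, associations with length of stay and with the four in-hospital segments (ABI/TBI, heparin, specialist, revascularization) are biased upward. The illustrative odds ratios are 1.13 to 1.51 under constant hazard, 1.17 for a 7- versus 21-day stay under a falling hazard, and about 1.2 per 7 days in the simulation. They rest on assumed stays, hazards and delay distributions.

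The effect is modest at 6 months and negligible at 12. It reaches pre-admission symptom duration only through a correlation with stay that the document does not quantify. Because the registry is a hypothesis-generating pilot and its main horizon is one year, this is a correction worth making and not a condition for the study to proceed.

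**What to change.** State index hospital arrival as time zero for all outcomes; the in-hospital segments already start there. Define short-term outcomes as events by day 30 from arrival and one-year amputation-free survival as events by day 365 from arrival, counting in-hospital events in both. Use the same origin for the Kaplan-Meier and Cox analyses.

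Take event dates from the medical records and the death index, not from the date of the call. Calls can stay scheduled from discharge, provided that record review extends to the full horizon when a call falls early in its window. Outcomes counted from discharge can be reported as a secondary description among patients discharged alive.

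The cost is a few sentences in the protocol and analysis text, plus abstraction of event dates from sources already being reviewed. Admission and discharge times are already needed for length of stay.
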